**Methods:**

PROACTIVE-19 is a pragmatic, randomised controlled clinical trial with adaptive “sample size re-estimation” design. Hungarian population over the age of 60 years without confirmed COVID-19 will be approached to participate in a telephone health assessment and lifestyle counselling voluntarily. Volunteers will be randomised into two groups: (A) general health education and (B) personalised health education. Participants will go through questioning and recommendation in 5 fields: (1) mental health, (2) smoking habits, (3) physical activity, (4) dietary habits, and (5) alcohol consumption. Both groups A and B will receive the same line of questioning to assess habits concerning these topics. Assessment will be done weekly during the first month, every second week in the second month, then monthly. The composite primary endpoint will include the rate of ICU admission, hospital admission (longer than 48 h), and mortality in COVID-19-positive cases. The estimated sample size is 3788 subjects per study arm. The planned duration of the follow-up is a minimum of 1 year.

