### Outcomes

Based on literature data [5, 26], the primary endpoint will be defined as the composite of any of the following in COVID-19 cases (an accredited laboratory should verify positivity), the rate of:
ICU admissionsHospital admissions (longer than 48 h) for the following reasons:
Arrhythmia (causing hemodynamic instability and requiring continuous monitoring and/or cardiac support, as indicated by mean arterial pressure < 65 mmHg, and/or serum lactate > 2 mmol/L)ARDS (severe hypoxaemic respiratory failure indicated by a PaO_2_/FiO_2_ < 300 mmHg according to the Berlin definition) [27]Circulatory shock (the requirement of continuous vasopressor support to maintain mean arterial pressure ≥ 65 mmHg and/or serum lactate ≤ 2 mmol/L)Deaths

Secondary endpoints are the following:
The number of general practitioner visitsThe number of emergency, hospital, and intensive care admissionsThe length of hospitalisation and ICU stayThe number of organ dysfunctions and failures (central nervous system, cardiovascular, respiratory, renal, liver, haematological)The measurable lifestyle changes (including physical and mental health)The costs of care

The primary and secondary outcomes will be assessed upon the conclusion of the trial, at least 1 year after the enrolment of the last participant.

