### Sample size calculation, interim, and final analyses

The primary outcome is estimated to occur in 20% of COVID-19-infected cases (≥ 60 years of age) receiving the standard of care based on Chinese reports [5]. Due to the lack of data, we hypothesised that our intervention would result in a 50% risk reduction. Considering one interim analysis on efficacy (with the Pocock correction), 90% power, 5% alpha (superiority design, two-sided), a dropout rate of 20% [28, 29], and assuming 10% incidence of COVID-19 in the target population, the estimated sample size is 3788 (rounded up to 3800) subject per study arm. The calculation was performed by Stata (version 15, Philadelphia, the USA).

We plan to hold three interim analyses: the first for sample size re-estimation at 5% of the target sample size due to the dropout rate, the second for safety assessment at 10% of the target sample size, and the third for efficacy assessment and sample size reestimation at 50% of the target sample size. Early stopping will be executed if (1) safety concerns arise during the interim analysis; (2) the statistical power reaches at least 90% and *p* < 0.05 at the efficacy interim analysis (stopping for benefit); (3) the statistical power does not reach 10%, *p* > 0.05, and the event number does not reach the assumed 10% for the whole population at the efficacy interim analysis (that is, 380 events for the primary outcome; otherwise, the interim analysis is postponed and repeated when the event number reaches 380 events) (stopping for futility); and (4) the consequences of the pandemic make further recruitment or follow-up impossible (stopping for unfeasibility).

In the final analysis, the intention-to-treat analysis will be favoured over per-protocol (or “as-treated”) analysis. We expect a full dataset for the primary endpoint (since the Hungarian Ministry of Interior will provide these data). If for any reason, data will be missing for the primary outcome, we will use available case analysis. The “last observation carried forward” strategy will be followed to impute missing data for other outcomes measured during the study. Missing more than one consecutive interventions after the initial assessment or withdrawal of consent during follow-up results in the dropout of the patients unless hospitalisation is required in the meantime.

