In descriptive statistics, the count and percentage will be provided for each treatment arm for binary outcomes. For continuous outcomes, *n*, mean, median, interquartile (Q3–Q1), standard deviation, minimum, and maximum values will be provided for each treatment arm. In a univariate comparative analysis, we will calculate relative risk with 95% confidence interval (CI) when comparing the primary endpoint between two groups (alpha = 5%) with a reference arm using non-repeated intervention complemented with chi-square or Fisher’s exact test (the same strategy will be followed for binary secondary outcomes). For continuous variables, we will use *t* test assuming unequal variances or the Mann-Whitney test. We will perform univariate (Kaplan-Meier and Cox-regression) and multivariate (Cox-regression) survival analysis for binary outcomes. An adjustment will be carried out at least for age, sex, and education. Mixed effect logistic regression will be conducted to estimate the effect of the multicomponent intervention on the outcomes, where the subject IDs will be used as a random subject. The model will be adjusted for changes in smoking habits, alcohol consumption, physical activity, and dietary habits (or body mass index).

All analyses will be carried out with SPSS version 26 and Stata version 15.

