### Study duration

The planned starting date of the study is 1 April 2020, and the anticipated finishing date is the end of the pandemic or development of the vaccine, but no more than 1 year from the enrolment of the last participant.

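### Visit counts, admission counts and costs build up over unequal follow-up, but the only non-binary tests named take no account of observed time; retention that differs by arm would then appear as an effect

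*Protocol article*

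**What the plan says.** The Outcomes section lists among the secondary endpoints the number of general practitioner visits, the numbers of emergency, hospital and intensive care admissions, and "The costs of care". Each grows with the time over which a participant is observed.

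That time is not the same for everyone. The abstract states "The planned duration of the follow-up is a minimum of 1 year". Outcomes are "assessed upon the conclusion of the trial, at least 1 year after the enrolment of the last participant", and Study duration sets the end at "the end of the pandemic or development of the vaccine, but no more than 1 year from the enrolment of the last participant". The two sections differ on whether 1 year after the last enrolment is a floor or a ceiling. Under either, the trial closes at one point for all, so early entrants are observed longer than late ones.

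The section on sample size and analyses assumes 20% dropout. It counts as a dropout anyone with "Missing more than one consecutive interventions after the initial assessment", or who withdraws consent, unless hospitalised in the meantime. Missing values of outcomes other than the primary are to be imputed by last observation carried forward (LOCF).

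For the comparison of arms, continuous variables get a t "test assuming unequal variances or the Mann-Whitney test". The survival models are reserved for binary outcomes and the mixed model is logistic. No rate, person-time, offset or fixed window is named.

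**The concern.** A t test or Mann-Whitney test on a participant's total does not know how long that participant was observed. No visits in a few weeks and no visits in more than a year enter as the same value.

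This has two consequences of unequal weight:

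- **Precision.** Variation in follow-up length adds noise to the totals. This happens even when both arms are observed equally long.
- **Bias.** If one arm is observed for less time on average, it shows fewer visits and lower costs with no true difference. LOCF does not repair this, because a running count carried forward stays frozen at its value on leaving.

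The first contact is expected to take about 20 minutes in group B and 10 in group A, so a retention difference is possible. If group B lost more participants, the error would favour the personalised intervention on health-care use and cost.

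**Working it through.** **The plan's own figure.** The documents give no sample size for the count or cost endpoints, only for the primary. That one reproduces: 20% against 10%, two-sided alpha 0.0294 per look (Pocock, two looks) and 90% power need 303 infected participants per arm, and 303 / 0.10 / 0.80 = 3787.5, i.e. 3788. The point below does not touch it.

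**Inputs.**
- From the protocol: 3800 per arm (rounded target), overall dropout 20%, minimum follow-up 1 year, common close.
- Assumed, because the protocol does not give them: uniform recruitment over 12 months with close 12 months after the last entry; visit rate r = 4 a year or admission rate r = 0.2 a year; between-person (gamma) variance k = 0.75; a proportion d of each arm leaving, uniformly over their scheduled time; dropout by arm of 18% v 22% or 15% v 25%, both averaging 20%.

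**Mean observed time.** Scheduled follow-up is uniform on 1 to 2 years, with mean 1.5 and mean square 7/3. With dropout,

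E(T) = 1.5 × (1 − d/2), E(T²) = (7/3) × (1 − 2d/3).

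- 18% v 22%: 1.365 v 1.335 years, ratio 0.978.
- 15% v 25%: 1.3875 v 1.3125 years, ratio 0.946.

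With no treatment effect, the ratio of mean totals equals these ratios. Totals therefore show a 2% or 5% reduction that is not there.

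**False positives of the t test on totals.** For a participant's count Y,

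E(Y) = r E(T), Var(Y) = r E(T) + r² [(1 + k) E(T²) − E(T)²].

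At r = 4 and 15% v 25%:
- Means are 5.55 and 5.25, a difference of 0.30.
- Variances are 5.55 + 16 × (1.75 × 2.100 − 1.925) = 33.55 and 5.25 + 16 × (1.75 × 1.944 − 1.723) = 32.13.
- Standard error = √[(33.55 + 32.13) / 3800] = 0.1315, so z = 0.30 / 0.1315 = 2.28.
- Probability of p < 0.05 is about Φ(2.28 − 1.96) = 63%.

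At r = 4 and 18% v 22% the difference is 4 × (1.365 − 1.335) = 0.12. With the same standard error z = 0.91, and the probability is about 15%. At r = 0.2 the same formulas give about 20% (15% v 25%) and about 7% (18% v 22%).

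**Simulation under no true effect**, which also covers the Mann-Whitney test and a rate analysis:

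| Assumed dropout, A v B | Outcome | t test | Mann-Whitney | Rate analysis |
|---|---|---|---|---|
| 20% v 20% | either | about 5% | about 5% | about 5% |
| 18% v 22% | 4 visits/year | 15–16% | 20–22% | 3–7% |
| 15% v 25% | 4 visits/year | 63–64% | 79% | 3–7% |
| 18% v 22% | 0.2 admissions/year | 6–7% | 6–7% | 3–7% |
| 15% v 25% | 0.2 admissions/year | 17–22% | 17–22% | 3–7% |

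The spread of 3–7% for the rate analysis is simulation noise.

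**Sensitivity to the dropout model.** The protocol does not say whether 20% is per year or overall. If it is a yearly rate with exponential leaving and recruitment lasts 0.5 to 1 year, 15% v 25% gives a ratio of totals of 0.91–0.93. False positives are then 78–99% (t) and 93–100% (Mann-Whitney) for visits, and 25–39% for admissions. The rate analysis remains near 5%.

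**Precision with equal dropout.** With a true rate ratio of 0.95 and 4 visits a year, power is 55–56% (t), 45–49% (Mann-Whitney) and 54–59% (rate model). Under the yearly dropout model, totals inflate the variance of the log ratio by 8–19% for visits and by about 2% for admissions.

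**The case against.** The strongest reply is that the article never says the counts are analysed as unscaled totals. It assigns the t test or Mann-Whitney test to continuous variables, does not class the counts among them, and may leave scaling to an analysis plan that is not shown. It stands that the use of totals is an inference. But the article does fix methods for its outcomes, these are the only ones that could apply to a count or a cost, and none of the other models covers them.

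Three stronger readings are tempting and are not supported.

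- *Unequal follow-up by itself creates a false effect.* It does not. Staggered entry is balanced by randomisation, and with equal dropout all methods reject at about 5%. How widely follow-up varies also depends on recruitment length, which is not stated.
- *The protocol implies that group B will lose more participants.* It gives one dropout figure for both arms, a matching call schedule, and an expectation that moderate intensity guards against poor adherence. The 20 and 10 minutes describe the first contact, and no length is given for later calls. The size and direction of any gap are unknown.
- *Observation ends when a participant drops out.* The protocol defines dropout without saying that all data collection stops, and the limitations section mentions indirect data sources besides the participants. The bias applies to data that do end with the calls.

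It is also fair that the bias arises through dropout and so overlaps with the choice of LOCF. That is why the remedy must address both.

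**Conclusion.** The concern holds in a conditional form. The named tests do not fit endpoints that accumulate over unequal time. With equal retention the price is small: a few points of power for visits and next to nothing for rare admissions. With unequal retention the error can be large for frequent events. A gap of 4 percentage points gives about 15–22% false positives for visits and 6–7% for admissions, and a gap of 10 points about 63–79% and 17–22%.

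These sizes rest on assumed event rates, between-person variance, recruitment length and dropout by arm. Costs were not simulated; the same reasoning applies because they too accumulate. The primary endpoint and its sample size are unaffected. The change is worth making before outcome data are seen, but it does not threaten the trial's main result.

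**What to change.** In the analysis text:

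1. Analyse numbers of visits and admissions with a negative binomial model (or quasi-Poisson with robust standard errors), with arm as factor and the log of observed time, from first call to death, last contact or study close, as offset. Report the rate ratio with its 95% confidence interval.
2. Do not apply LOCF to cumulative counts.
3. Compare costs over a common window, or with a method that allows for censoring.
4. Keep the t test and Mann-Whitney test for outcomes that do not accumulate with follow-up.
5. Report observed time by arm, so that any difference in retention can be seen.

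The cost is a change of wording in the analysis plan. The scheduled calls should supply the dates needed, and sample size and conduct are unchanged.

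The downside is that a rate model assumes a roughly constant event intensity and that leaving is unrelated to it. The exemption of hospitalised participants from the dropout rule strains the second assumption. In a simulation where frailer participants left differently, rejection by the rate model rose to about 10%, still better than totals. The model reduces the bias but may not remove it.

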## Background

World Health Organization (WHO) announced the coronavirus disease 2019 (COVID-2019) outbreak pandemic in the morning of 12 March 2020 [1]. At the time of writing this study protocol, there are more than 770,000 confirmed cases with 37,000 fatalities across 178 countries, according to the Center For Systems Science and Engineering (CSSE) at Johns Hopkins University, including 447 cases and 15 deaths in Hungary. The tendency predicts that the epidemic is far from its peak [2].

As often seen in the case of other epidemics, most cases can be asymptomatic or develop only mild symptoms and remain undiagnosed. Therefore, it is difficult to estimate the true incidence and the disease outcomes precisely [3, 4]. However, early reports indicate that it may require intensive care unit (ICU) admission in 5–26%, due to acute respiratory distress syndrome (ARDS) in 17–20%, and overall mortality can rise to 11% of the recognised cases, mostly affecting the elderly [5–8]. These numbers are comparable to the outcomes of earlier coronavirus epidemics [9, 10] and more severe than H1N1 pandemics in 2009 [11].

Significant efforts have been invested in research and development to re-target existing and discover new pharmacological treatments and preventive strategies against COVID-19 [12], as indicated by the number of submitted protocols of the currently recruiting randomised trials on ClinicalTrials.gov. Nevertheless, it must be noted that we lack evidence-based targeted pharmacological therapy for prevention and treatment alike [13]. None of the registered studies investigates the effects of lifestyle interventions in the prevention of poor outcomes in the COVID-19 epidemic. Advanced age and pre-existing comorbidities, such as cancer, cardiovascular disease, or diabetes mellitus, predispose to a more severe disease course and ICU admission [6, 14–16].

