### Randomisation and blinding

Computer-generated random sequence randomisation (central) will be performed, after giving informed consent. Due to the expected large sample size, we will use simple randomisation. The allocation ratio will be 1:1. No stratification or blocking will be applied.

In the study, participants will be blinded to the knowledge of the details of differences between the interventions. Everyone else (outcome assessors, caregivers, and data analysts) will be blinded regarding the allocation.

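### The primary endpoint is tested by an unadjusted relative risk, and the plan does not say whether this or the baseline-adjusted model decides the trial; adjusting it would be a modest, free gain

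*Protocol article*

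**What the plan says.** All analysis statements are in the protocol article, Methods, under Sample size calculation, interim, and final analyses.

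- **Primary endpoint:** "In a univariate comparative analysis, we will calculate relative risk with 95% confidence interval (CI) when comparing the primary endpoint between two groups". The same sentence gives alpha as 5% and adds a chi-square or Fisher's exact test. This is the only analysis explicitly linked to both the primary endpoint and an alpha.
- **Survival models:** the next statement on binary outcomes plans Kaplan-Meier and both univariate and multivariate Cox regression. It is followed by "An adjustment will be carried out at least for age, sex, and education". The adjustment sentence stands alone, and no analysis is labelled primary or secondary.
- **A further model:** a mixed-effect logistic regression is adjusted for changes in lifestyle during the trial.

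Randomisation and blinding specifies simple 1:1 allocation because a large sample is expected: "No stratification or blocking will be applied". The Outcomes section counts the composite only in laboratory-confirmed COVID-19 cases. The Background states: "Advanced age and pre-existing comorbidities, such as cancer, cardiovascular disease, or diabetes mellitus, predispose to a more severe disease course and ICU admission".

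**The concern.** Two things are at stake.

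**Which result decides.** A crude relative risk and an adjusted hazard ratio for the same composite will both be reported. If one crosses its threshold and the other does not, the article gives no rule. A reader could not tell whether the disagreement came from the covariates or from the change of effect measure.

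**Unused precision.** The article names age, sex and education for adjustment and says that age matters for severity, yet the comparison that carries the alpha uses none of them. The large-sample reason for not stratifying applies to all participants randomised. The analysed set is the infected, roughly a tenth of that number or less, where chance imbalance in age is larger. Adjusting the deciding comparison would recover some power and would stop a chance age difference from passing straight into the reported relative risk.

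**Working it through.** **1. Reproduce the sample size.** Inputs from the article: "The primary outcome is estimated to occur in 20% of COVID-19-infected cases"; "we hypothesised that our intervention would result in a 50% risk reduction", so 20% v 10%; 90% power; 5% two-sided with one Pocock efficacy look (nominal 0.0294 per look, z = 2.178); 20% dropout; 10% infected.

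n per arm = [2.178 × √(2 × 0.15 × 0.85) + 1.282 × √(0.20 × 0.80 + 0.10 × 0.90)]² / 0.10²
= [2.178 × 0.505 + 1.282 × 0.500]² / 0.01 ≈ 303 infected and evaluable.

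303 / 0.80 / 0.10 = 3787.5, that is 3788 per arm, the stated figure. The sample size therefore rests on the unadjusted two-proportion test, and that test has 90.0% power with 303 per arm.

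**2. Size of the analysed set.** 2 × 303 = 606. Expected events are 303 × 0.20 + 303 × 0.10 ≈ 91. The article also expects complete primary-endpoint data from a ministry source. If dropout then costs nothing, the set is 2 × 3800 × 0.10 = 760, and unadjusted power at 380 per arm is about 95.5%.

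**3. Chance imbalance.** The 95% range of a standardised covariate difference is ±1.96 × √(2/n per arm).

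- All randomised: 1.96 × √(2/3788) = 0.045 SD.
- Infected: 1.96 × √(2/303) = 0.159 SD, about 3.5 times as large.

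If the covariate has odds ratio OR per SD, an imbalance at that limit multiplies the crude odds ratio by about OR^0.159. This gives 1.07 for OR 1.5, 1.12 for OR 2 and 1.19 for OR 3. An imbalance at least this large, in either direction, arises in about 1 trial in 20.

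**4. Power with adjustment.** The article gives no covariate strength, so a range is assumed. The simulations use N = 606, simple 1:1 allocation and nominal alpha 0.0294.

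Chi-square v logistic regression adjusted for one baseline score (5,000 trials per row; OR per SD = exp of the log-odds slope 0, 0.5, 0.8, 1.0, 1.5):

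| OR per SD | AUC | 20% v 10%: crude, adjusted | 20% v 13%: crude, adjusted |
|---|---|---|---|
| 1.0 | 0.50 | 90.2%, 89.9% | 55.8%, 55.2% |
| 1.65 | 0.64 | 90.0%, 91.0% | 55.5%, 56.1% |
| 2.2 | 0.70 | 90.5%, 92.6% | 56.1%, 58.9% |
| 2.7 | 0.74 | 90.8%, 93.3% | 55.8%, 61.8% |
| 4.5 | 0.82 | 90.7%, 95.8% | 56.6%, 68.6% |

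The last row lies beyond the range relied on here.

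For the estimator proposed below, a relative risk standardised from the logistic model, the gain over the chi-square at 20% v 10% is about 0 points for OR 1.5, 1 to 2 for OR 2 and 3 to 4 for OR 3. At 20% v 13% it reaches about 6 points for OR 3.

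**5. Type I error.** Under no effect (AUC 0.74), the chi-square rejected in 3.15% of trials and the adjusted logistic test in 3.16% (Monte Carlo SE about 0.17 points). The standardised relative risk also left type I error unchanged.

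**6. Why Cox is not the same analysis.** Even with no covariates, and assuming proportional hazards and equal follow-up, risks of 20% and 10% give a hazard ratio of ln(0.90)/ln(0.80) = 0.105/0.223 = 0.47, against a relative risk of 0.50.

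**The case against.** The strongest reply is that nothing here is an error. The crude comparison is valid under randomisation, matches the sample-size method and meets its stated power. Chance imbalance is part of the sampling variation that its confidence interval already covers. Adjusted Cox regression is planned for binary outcomes, which include the composite, and Data handling says baseline similarity will be checked. The gain rests on an assumed covariate strength. The upper end may be generous for a score that is mostly age in people already over 60, and with a useless covariate the gain is nil. An unseen analysis plan may also settle the covariates. All of this stands as a limit on the size of the point.

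Four stronger readings that a reader might infer are not supported:

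- **That age, sex and education enter only a secondary model.** The article labels nothing secondary and does not expressly confine the adjustment sentence to Cox.
- **That protection against imbalance is given up altogether.** An adjusted estimate for the composite is planned.
- **That the trial is underpowered without adjustment.** It has 90.0% power on its own inputs, and more if registry data are complete.
- **That imbalance invalidates the test.** Type I error is unaffected.

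What the reply does not answer is that the article itself fixes the crude relative risk as the alpha-bearing comparison, places an adjusted result on a different scale beside it, and does not say which one governs.

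**Conclusion.** The point holds as a modest, nearly free improvement together with an ambiguity to close. It is not a validity flaw. The article ties the primary endpoint and alpha to an unadjusted test, follows it with baseline adjustment attached most naturally to a model of a different quantity, and ranks neither.

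The precision left unused is worth about 0 to 4 power points at the design effect. It is worth up to about 6 points if the effect is nearer 20% v 13%, which matters because the article says the 50% reduction was chosen for lack of data. These figures assume a baseline prognostic odds ratio of 1.5 to 3 per SD, about 606 analysed participants and the nominal Pocock level. With about 760 analysed, unadjusted power at the design effect is already about 95.5%, so less remains to be gained there.

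**What to change.** Name one primary analysis of the composite: a relative risk with 95% confidence interval, standardised from a logistic model containing arm and baseline age (continuous), sex and education. Modified Poisson regression with robust standard errors is an acceptable alternative. Test it at the plan's group-sequential level at both the efficacy interim and the final analysis. Keep the crude relative risk with chi-square or Fisher's exact test, and the Cox model, as supportive.

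Two limits should be written in. Changes in lifestyle after randomisation must stay out of this model, because they may be effects of the intervention. Baseline adjustment also does not remove any selection that comes from analysing only people who became infected after randomisation.

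The cost is a sentence or two in the analysis section. The covariates are already named for adjustment, about 91 expected events can carry so small a model, and neither new data nor a change in sample size is needed.
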